# Design and Organization of the Dexamethasone, Light Anesthesia and Tight Glucose Control (DeLiT) Trial: a factorial trial evaluating the effects of corticosteroids, glucose control, and depth-of-anesthesia on perioperative inflammation and morbidity from major non-cardiac surgery

**DOI:** 10.1186/1471-2253-10-11

**Published:** 2010-06-30

## Abstract

**Background:**

The perioperative period is characterized by an intense inflammatory response. Perioperative inflammation promotes postoperative morbidity and increases mortality. Blunting the inflammatory response to surgical trauma might thus improve perioperative outcomes. We are studying three interventions that potentially modulate perioperative inflammation: corticosteroids, tight glucose control, and light anesthesia.

**Methods/Design:**

The DeLiT Trial is a factorial randomized single-center trial of dexamethasone vs placebo, intraoperative tight vs. conventional glucose control, and light vs deep anesthesia in patients undergoing major non-cardiac surgery. Anesthetic depth will be estimated with Bispectral Index (BIS) monitoring (Aspect medical, Newton, MA). The primary outcome is a composite of major postoperative morbidity including myocardial infarction, stroke, sepsis, and 30-day mortality. C-reactive protein, a measure of the inflammatory response, will be evaluated as a secondary outcome. One-year all-cause mortality as well as post-operative delirium will be additional secondary outcomes. We will enroll up to 970 patients which will provide 90% power to detect a 40% reduction in the primary outcome, including interim analyses for efficacy and futility at 25%, 50% and 75% enrollment.

**Discussion:**

The DeLiT trial started in February 2007. We expect to reach our second interim analysis point in 2010. This large randomized controlled trial will provide a reliable assessment of the effects of corticosteroids, glucose control, and depth-of-anesthesia on perioperative inflammation and morbidity from major non-cardiac surgery. The factorial design will enable us to simultaneously study the effects of the three interventions in the same population, both individually and in different combinations. Such a design is an economically efficient way to study the three interventions in one clinical trial vs three.

**Trial registration:**

**This trial is registered at **Clinicaltrials.gov **#**: NTC00433251

## Background

Mortality remains substantial among high-risk patients (ASA physical status 3-5)[1]. In some populations, it is estimated to be as high as 5-14% during the first postoperative year[2-4]. Efforts to identify interventions that decrease perioperative morbidity and mortality are thus warranted. The perioperative period is characterized by an intense inflammatory response marked by elevated concentrations of inflammatory markers like C-Reactive Protein (CRP). Inflammation is the body's response to tissue injury[5] and results in production of inflammatory mediators[6], which are associated with considerable postoperative morbidity. For example, cardiovascular mortality is responsible for 17% of post-operative deaths[3]. Inflammation has been an important mediator in the pathophysiology of myocardial infarction, at all stages in the development of vulnerable plaque, from initial lipid deposition to plaque rupture. Thus, markers of systemic inflammation such as CRP may better predict perioperative cardiac morbidity and mortality than currently utilized strategies[7]. Furthermore, there is an important link between inflammation and poor perioperative outcomes[7,8]. Thus interventions that moderate the inflammatory response may prove to reduce adverse outcomes[9].

Many anti-inflammatory therapies have been tested in the perioperative period. The anti-inflammatory effects of corticosteroid are well established[10]. High doses of methylprednisolone or dexamethasone are important biologic modifiers of perioperative inflammatory responses in cardiac surgical patients, and reduce perioperative organ dysfunction[11]. Similarly, in non-cardiac surgery, high-dose steroids reduce the inflammatory response and improve outcomes[12,13]. Enthusiasm for use of corticosteroids in cardiac surgery has been dampened by concerns over the potential risks of such large doses. However, two major reviews concluded that a single large dose of corticosteroids appears to be harmless in the absence of specific contraindications[11,14]. Moreover, Kilger et al. observed a significant reduction in circulating inflammatory marker concentrations, along with improved outcomes after a small dose of hydrocortisone[15]. And finally, in a randomized trial of patients undergoing laparoscopic cholecystectomy, 8 mg of dexamethasone resulted in significantly lower CRP levels, significantly reduced postoperative fatigue and postoperative nausea and vomiting (PONV), and a faster return to recreational activities[16].

Another factor influencing the surgical stress response and inflammation, and thus postoperative outcomes, is anesthetic management[17]. For example, deep anesthesia may be associated with adverse outcomes including mortality. Lennmarken et al. showed that duration at deep anesthetic levels (BIS < 45) was significantly related to 1-year mortality, increasing it by 20% per hour,[2] and that non-survivors spent more time at deep BIS levels than the survivors[18]. In a cohort of adults having non-cardiac surgery under general anesthesia, lower BIS levels were independently associated with higher mortality[3]. In this study, most deaths were attributed to either cancer or cardiovascular etiologies, the pathogenesis of which has been well linked to inflammation[19-21]. The authors postulated that prolonged deep anesthesia increases mortality by aggravating the inflammatory response to surgery[3]. In support of that theory, a pilot study in orthopedic joint replacement patients demonstrated that patients who received BIS-guided anesthesia (target 45-60) showed a reduced post-operative inflammatory CRP response compared to deeper standard clinical practice[22].

Hyperglycemia is a physiologic response to surgical stress and is associated with adverse outcomes[23] such as impaired wound healing and increased infection risk. Surgical patients and those suffering acute illnesses often develop hyperglycemia, even in the absence of a preexisting diabetes[24]. Hyperglycemia is pro-inflammatory and provokes release of inflammatory cytokines. Fasting blood glucose concentration is independently related to CRP levels[25]. On the other hand, insulin *per se *is anti-inflammatory and might thus prove beneficial[26,27]. Van den Berghe et al. showed in a prospective randomized trial that intensive insulin therapy to maintain blood glucose at or below 110 mg/dL decreased inflammatory markers, and significantly reduced overall hospital mortality, blood stream infections, and acute renal failure among patients in the surgical intensive care unit (ICU)[28]. Normoglycemia also significantly reduced the use of catecholamines, and improved long-term rehabilitation[29].

The use of normoglycemia or tight glucose control is not well established in the perioperative period. In a study in cardiac surgical patients, continuous intravenous insulin infusion reduced the incidence of deep sternal wound infection and reduced mortality in diabetic patients[30,31]. But in another single-center randomized trial in a similar patient population, tight glycemic control intraoperatively did not improve outcomes,[32] although there was a relatively small difference in blood glucose concentrations in the two groups. Furthermore all patients received intensive glucose control in the ICU following their surgery, which may have lessened the effects of intraoperative glucose control[33].

The effects of intraoperative intensive vs conventional glucose control on perioperative outcomes in major non-cardiac surgery remain unknown. Normoglycemia might decrease postoperative complications such as respiratory, cardiovascular, renal and neurologic events. One outcome which has not been studied in the context of tight glucose control is postoperative delirium. Postoperative delirium is common after certain surgical procedures with a reported incidence as high as 20-60%[34]. Delirium is an important complication as it significantly impacts postoperative recovery[35]. The pathogenesis of delirium remains poorly understood, but there are reasons to believe that inflammation contributes. In vascular surgery patients, higher preoperative CRP concentrations augment the probability of postoperative delirium[35]. In hip fracture surgery, CRP concentrations were significantly greater in delirious vs. nondelirious patients [36]. And finally, intraoperative glucose concentrations were significantly greater in cardiac surgical patients experiencing a primary composite outcome that included delirium[23].

Available evidence suggests that blunting the inflammatory response to surgical trauma might improve perioperative outcomes. The putative benefits from blunting the surgical stress response are likely to be greatest in high-risk patients such as those having major non-cardiac surgery. We are thus studying three interventions potentially modulating perioperative inflammation, corticosteroids, tight glucose control and light anesthesia and their effects on major morbidity and mortality resulting from major non-cardiac surgery.

### Primary hypotheses

major perioperative morbidity in patients having major non-cardiac surgery is reduced by: 1) low-dose dexamethasone; 2) intensive intra-operative glucose control; and 3) lighter anesthesia.

### Secondary hypotheses

each intervention reduces circulating concentrations of the inflammatory marker CRP; CRP concentration correlates with post-operative complications; anesthetic sensitivity predicts major and minor complications, including delirium. Other secondary hypotheses are that each intervention reduces minor surgical complications, reduces PONV, reduces postoperative delirium, speeds hospital discharge, improves quality of life (SF-12v2 Health Survey, Christensen's VAS fatigue score), and reduces all-cause one-year mortality.

## Methods/Design

### Setting and Population

Patients scheduled for elective major non-cardiac surgeries at Cleveland Clinic will be evaluated during their preoperative anesthesia clinic visits:

#### Inclusion Criteria

1) Age ≥40 years old;

2) Major non-cardiac surgical procedures;

3) Written informed consent.

#### Exclusion Criteria

1) Recent intravenous or oral steroid therapy (within 30 days); inhaled steroids are permitted;

2) Any contraindications to the proposed interventions;

3) ASA Physical Status > 4;

*4*) Procedures done under regional anesthesia.

#### Ethics

The study protocol has been reviewed and approved by the Cleveland Clinic Institutional Review Board (IRB # 07-010)

### Study Protocol

Patients will be randomly assigned to *each *of the following interventions:

1) **Intravenous Dexamethasone or placebo**: 8 mg of dexamethasone (or placebo) will be given 1-2 hours before incision, 4 mg on the first postoperative morning, and 2 mg on the second postoperative morning.

2) **Intensive or conventional glucose management**: Patients will be randomized to blood glucose concentrations of 80-110 mg.dL^-1 ^(intensive control with a specific algorithm) or 180-200 mg.dL^-1 ^(conventional control). Glucose control will begin shortly after induction of anesthesia using pre-designed protocols and continue through the first 2 hours of postanesthesia care unit (PACU) stay. Patients will then follow the routine of the ICU/hospital ward where they will be admitted.

3) **Lighter or deeper anesthetic management**: Patients will be assigned to a target BIS of 55 (lighter anesthesia group) or 35 (deeper anesthesia group)

Randomization will be generated by a web-based system that will be accessed before anticipated induction of anesthesia, and will be stratified by history of diabetes.

Patients may be premedicated with intravenous midazolam. Prophylactic antibiotics will be given per surgical routine. General anesthesia will be induced with fentanyl and propofol. Tracheal intubation will be facilitated by succinylcholine or a non-depolarizing muscle relaxant. Additional non-depolarizing muscle relaxants will be given as necessary. Anesthesia will be maintained with sevoflurane in O_2 _and air combined with a fentanyl infusion; anesthetic drugs will be managed based on the randomized strategy; that is a BIS near 35 or 55. The lungs will be mechanically ventilated to maintain end-tidal PCO_2 _near 35 mmHg. Normothermia will be maintained with forced-air warming[37]. Blood pressure will be controlled to within a range of +20% to -30% of the preoperative baseline value. Heart rate will be controlled within a range of 40-90 beats/minute.

Red blood cell transfusions are immunosuppressive[38]. Red cell transfusions will thus be controlled by protocol. Target minimum hematocrits (HCT) will be determined based on the patient's cardiovascular status. The HCT will be maintained at 25-28% in patients without substantial cardiac disease, but maintained at 30% in those with significant cardiac disease, defined as previous myocardial infarction, angina, congestive heart failure, or cardiomyopathy.

### Measurements

We will record demographic data, ASA physical status, medical history, drug usage, preoperative hemoglobin and hematocrit, BUN and creatinine, electrolytes, and pre-operative electrocardiogram. A BIS sensor will be applied to the forehead before induction and connected to a BIS monitor. Anesthetic data will include: the volatile anesthetic dose in MAC-hours, as well as total doses of propofol and other sedative hypnotics. Distal esophageal temperature will be recorded. Blood loss will be estimated; urine output and fluid administration including allogenic blood will be recorded. Blood pressure and heart rate will be recorded. Automated intra-operative ST segment values will be recorded every 15 minutes. BIS values will be recorded electronically at one-minute intervals. Perioperative use of antibiotics and intraoperative vasoactive drugs will be recorded.

We will record the admission glucose concentration and at least hourly glucose concentrations during surgery and during the first two postoperative hours; the results of any additional glucose determinations throughout the hospital stay (obtained for clinical purposes) will also be recorded. We will use previously described methodologies to determine efficacy and safety of the insulin infusion protocols, including proportion of time spent within target range and number of hypoglycemic episodes (< 40 mg.dL^-1^)[39]. We will also measure time-weighted average (TWA) glucose and time taken to achieve desired level of glucose control. We will compare our results to other published findings in similar trials; the closest to our trial is that of Gandhi et al who investigated almost the same targets in their randomized trial in cardiac surgery patients[32]. The time to PACU discharge will be recorded, along with days in the ICU if applicable, duration of postoperative mechanical ventilation in hours, total post-operative opioid use, and the duration of hospitalization in days. Blood for high-sensitivity CRP, creatinine phospho-kinase and cardiac troponin T measurements will be sampled at the time of induction, at post-operative day 1 and 2. A 12-lead electrocardiogram will be performed immediately post-operatively and the subsequent morning.

We will use the Confusion Assessment Method (CAM) as it is the most commonly used tool in the study of delirium. It is easily performed, has a sensitivity of 94% to 100% and a specificity of 90% to 95%[40]. Christensen's fatigue VAS [41] is one of the most widely used measures of postoperative fatigue. The test will be administered pre-operatively and on post-operative days 1 and 3. An increase of three or more units on the 10- point scale will be considered a clinically significant increase.

### Data Analysis

Our primary outcome is the occurrence of at least one major complication (Table 1) in a patient within the same hospitalization and 30-day mortality. Our composite is a minor modification of the composite outcome used by Brandstrup et al.[42] and Nisanevich et al.[43]. The use of a composite adverse outcome indicator rather than independently evaluating specific complications likely reduces the chance of Type 2 error. More importantly, using any single outcome may not capture the entire effect of any of our interventions or the complex disease processes. All analyses will be intention-to-treat.

**Table 1 T1:** Components of the composite primary outcome

Major Complications	Requirements for acceptance
Deep or organ/space surgical site infection	CDC criteria[49]
Sepsis	Positive blood culture and at least two of the following: Hypo or hyperthermia, tachycardia, tachypnea, leucopenia/leukocytosis ± DIC or multiorgan dysfunction
Bowel and surgical anastomosis stricture/obstruction or anastomotic leak	Requiring surgical intervention
Vascular graft thrombosis	Requiring surgical intervention
Bleeding	Requiring transfusion > 4 units of RBCs within the first 72 hours after surgery
Large peritoneal/pleural effusion	Diagnosed by X-Ray, ultrasound, and/or aspiration, and requiring chest tube, surgery, or ICU admission
Internal or external fistula formation	Requiring intervention
Stroke	New focal neurologic deficit of presumed vascular etiology persisted more than 24 hr with a neurologic study that did not indicate a different etiology
Pulmonary emboli (PE)	Sudden death or confirmation by V-Q scan showing high probability for PE, spiral CT scan or pulmonary arteriogram
Pulmonary edema and congestive heart failure	Shortness of breath, crepitation, peripheral edema and third heart sound and radiologic signs (cardiomegaly, interstitial edema, alveolar edema), medical treatment with diuretics
Myocardial infarction	ECG changes and/or elevated myocardial enzymes (cTn-T ≥0.2 ng/mL and/or CK ≥170IU and MB ≥5%)
Ventricular arrhythmias	ECG changes requiring medical treatment and/or electro-conversion
Renal failure	Requiring dialysis
Mortality	All-cause death within 30 postoperative days
Respiratory failure	Requiring intubation for more than 3 days
Pneumonia	New infiltrate on CXR combined with 2 of the following: temperature > 38°C, leukocytosis, and positive sputum or bronchial culture

CDC = Center for Disease Control; DIC = Disseminated Intravascular Coagulopathy; ICU = Intensive Care Unit; VQ = Ventilation Perfusion; CT = Computed Tomography; ECG = Electrocardiogram; CXR = Chest X-Ray

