#### Additional outcomes

Time-to-event outcomes (e.g., time to death, hospital LOS, and ICU LOS) will be analyzed using Cox regression, while binary outcomes (e.g., minor perioperative complication composite (Table 2), delirium, and PONV) will be analyzed using logistic regression, and continuous variables (including SF-12) using linear regression or a non-parametric alternative. Additional analyses will be performed adjusting for any baseline potentially confounding factors for which clinical imbalance between randomized groups is observed. The significance level will be 0.05 for all main effect hypotheses, and 0.10 for interactions. Table 3 summarizes the timing of interventions and outcomes' measures.

**Table 2 T2:** Minor Complications

Complication	Requirements for acceptance
Superficial incisional surgical site infection, or hematoma	Surgical evacuation of hematoma and or CDC
Intra-operative ST segment ischemia	An ischemic episode is defined as an ST segment change showing either ≥ 1 mm depression or ≥ 1.5 mm elevation from baseline
Unplanned ICU admission	Unplanned ICU admission
Minor surgical intervention	Surgeon called for care issues during the first 2 hours postoperatively
Non-ventricular arrhythmias	ECG changes, medical Rx and/or electroconversion
Small peritoneal/pleural effusion	Diagnosed by X-Ray, ultrasound, and/or aspiration, and not requiring chest tube, surgery, or ICU admission
Ileus	Lasting more than 72 hours
DVT	Diagnosed by Doppler examination, venogram, or CT scan
Cystitis or urinary tract infection	Fever, dysuria and positive urine culture
Hemodynamic disturbances	Requiring vasoactive drugs and/or β blocker treatment in the first 2 hours postoperatively
Progressive renal insufficiency	Rise in creatinine of > 2 mg/dl from pre-operative value but with no requirement for dialysis

CDC = Center for Disease Control; ICU = Intensive Care Unit; DVT = Deep Venous Thrombosis; Rx = treatment; ECG = Electrocardiogram; CT = Computed Tomography

**Table 3 T3:** Flow -chart of timing of the interventions and outcomes measures

	Pre-op visit	Preop Immediate	Intra-op	Post-op immediately	POD1	POD2	POD3	Hospitalization	30-day	6, 12 months
		Dexamethasone (8 mg)			Dexamethasone (4 mg)	Dexamethasone (2 mg)				
	
**Interventions**			Depth of Anesthesia							
	
			Glucose Control	Glucose Control						

										

								Composite Primary outcome	Primary outcome (mortality)	
	
								Secondary outcomes	Secondary outcomes	Secondary outcomes
	

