	SF-12								SF-12	
	
**Outcomes**	Christensen Fatigue Score				Christensen Fatigue Score		Christensen Fatigue Score			
	
					CAM ICU - twice daily	CAM ICU - twice daily	CAM ICU - twice daily			
	
									Phone call- vital status	Phone call- vital status
	
	EKG			EKG	EKG					
	
				Cardiac Enzymes 3 × 8 hrs apart						
	
		CRP			CRP	CRP				

POD = post operative day; SF 12 = health-related quality of life measure; CRP = C-Reactive Protein; CAM ICU =Confusion Assessment Method-ICU

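### The myocardial infarction component of the primary composite is not tied to the baseline ECG or induction enzymes, and the enzyme sampling schedule is stated in two incompatible ways

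*Protocol article*

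**What the plan says.** The Data Analysis section defines the endpoint: "Our primary outcome is the occurrence of at least one major complication (Table 1"), or death within 30 days. One Table 1 item is therefore enough to make a patient a primary event.

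For myocardial infarction, Table 1 requires "ECG changes and/or elevated myocardial enzymes (cTn-T ≥0.2 ng/mL and/or CK ≥170IU and MB ≥5"%).

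On baseline data, the Measurements section records a "pre-operative electrocardiogram". It adds: "A 12-lead electrocardiogram will be performed immediately post-operatively and the subsequent morning". For enzymes it says: "creatinine phospho-kinase and cardiac troponin T measurements will be sampled at the time of induction, at post-operative day 1 and 2".

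Table 3, the timing chart under Additional outcomes, describes enzyme sampling as "Cardiac Enzymes 3 × 8 hrs apart", entered in the column for the period immediately after surgery.

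Table 2 defines the minor complication of intraoperative ST ischemia by "≥ 1 mm depression or ≥ 1.5 mm elevation from baseline".

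**The concern.** The acceptance rule for infarction uses neither of the two baselines that the plan collects. A patient whose troponin T was already at the limit at induction meets the criterion on any later sample that is still at the limit. An ECG change of no stated kind or size meets it too, and every patient has two scheduled postoperative tracings. The minor ST-ischemia item is held to a stricter standard than this major one.

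The two enzyme schedules make this worse. Only the one in Measurements contains a baseline value, so only under that one can a pre-existing elevation be recognised. The schedules also look at different times, so they will not find the same enzyme events.

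At stake is the sharpness of the primary composite. Events already present before treatment, or unrelated to ischemia, carry little or no treatment effect and pull the comparison toward no difference.

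**Working it through.** **1. Routes to a primary event in the infarction row, as printed**

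| Route | What is needed | Baseline reference |
|---|---|---|
| ECG | changes, with no pattern, size or persistence given | none named |
| Troponin T | at least 0.2 ng/mL, alone | none |
| CK with MB | CK at least 170 IU and MB at least 5%, together | none |

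Other rows do carry such a qualifier. In Table 1 the stroke deficit and the pneumonia infiltrate must be new, and ventricular arrhythmias must need treatment. In Table 2 the ST item has a millimetre threshold relative to baseline.

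**2. The enzyme schedules side by side**

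| | Measurements | Table 3 |
|---|---|---|
| Baseline | at induction | none |
| After surgery | day 1 and day 2 | three samples, spanning 2 × 8 = 16 hours |

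A shifted table column cannot explain the difference, because the words in the Table 3 cell cannot describe induction, day 1 and day 2. The CRP and ECG rows of Table 3 agree with Measurements, so the disagreement is confined to the enzyme row. No sentence says that the two schedules are to be added together.

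**3. The plan's own sample size, reproduced as a base for the illustration**

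Inputs from Sample size considerations: 25% with no intervention; relative reductions of 40%, 20% and 10%; 90% power; 0.05; a maximum of 970. Assumed: a two-sided test and 1:1 allocation for each factor.

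- In a factorial comparison, half of each arm also receives each of the other two interventions. The marginal control rate is 0.25 × (1 − 0.20/2) × (1 − 0.10/2) = 0.25 × 0.90 × 0.95 = 0.21375.
- The marginal treated rate is 0.60 × 0.21375 = 0.12825.
- n per arm = [1.960·√(2·p̄·(1 − p̄)) + 1.282·√(p₁(1 − p₁) + p₂(1 − p₂))]² / (p₁ − p₂)², with p̄ = 0.171. This is (1.0436 + 0.6780)² / 0.0855² ≈ 405.4, so 406 per arm and 812 in total.
- The inflation factor for four equally spaced looks (efficacy gamma −3, futility gamma 0, non-binding) is 1.215 by numerical integration, giving about 986. That is within 2% of 970. The same boundaries give efficacy p-values of 0.0029, 0.0070, 0.0171 and 0.0407, which match the stated ones.

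**4. Illustration of dilution**

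Let f be the share of true non-events wrongly accepted as infarction, equal in both arms and unaffected by treatment. The documents give no value for f. The observed rate is p + f(1 − p).

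| f (assumed) | Control | Treated | Risk ratio |
|---|---|---|---|
| 0 | 0.2138 | 0.1283 | 0.600 |
| 2% | 0.21375 + 0.78625 × 0.02 = 0.2295 | 0.12825 + 0.87175 × 0.02 = 0.1457 | 0.635 |
| 5% | 0.2531 | 0.1718 | 0.679 |
| 10% | 0.2924 | 0.2154 | 0.737 |

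**The case against.** The right-hand column of Table 1 lists what is needed to accept the diagnosis named on the left. On that reading the infarction row sets out supporting evidence and does not turn every oddity on a routine tracing into an infarction. The word for change also suggests comparison with an earlier ECG, and detailed adjudication rules may sit in the full protocol. This has some force for the ECG route: a sensible assessor would not accept everything. But the row gives that assessor no criterion and names no reference tracing. The enzyme limits are absolute values, to which the argument does not apply. The rule and both schedules are printed, so the point concerns what is stated and not what is left out.

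Four stronger readings are tempting, and the documents do not support them.

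- A reader might infer a definite loss of power. Applied to 970 patients, the same values of f give roughly 86–87%, 80–81% and 71–72%, depending on how the sequential boundaries are handled. These figures rest wholly on the assumed f. They add the false events on top of the 25%, although that rate and the 40% reduction are both stated for this same composite. If both were estimated under this definition, the false events are already inside them and the planned ratio of 0.60 stands. They also assume no treatment effect on any added event. That fits elevations present before surgery, but it is unproven for new postoperative changes.
- A reader might infer that any single raised enzyme is enough. That is true of troponin T only; CK and MB are required together.
- A reader might infer bias in favour of an arm. The Limitations section blinds the collectors of postoperative events to all three assignments, so error should be similar in both arms.
- A reader might conclude that enzyme and ECG or clinical evidence should both be required. That would drop infarctions detected by enzymes alone, a debatable trade-off that nothing in the documents settles.

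**Conclusion.** Two defects stand on the printed text. The infarction rule does not require a finding to be new relative to the preoperative ECG or the induction enzymes, so pre-existing elevations and non-specific ECG changes can be counted as primary events. The enzyme schedules in Measurements and Table 3 contradict each other, and under Table 3 no baseline enzyme exists.

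Because outcome collection is blinded, the expected consequence is non-differential dilution toward the null. The documents do not allow its size to be estimated. The risk ratios of about 0.64, 0.68 and 0.74 are illustrations that depend on the assumed f, on equal error in both arms and on no treatment effect on the miscounted events. They are not estimates for this trial. No figure here measures the effect of the schedule conflict. Infarction is one of 16 components, and the planned sample size is not in dispute.

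**What to change.** - Reconcile Measurements and Table 3 into one enzyme schedule that applies to every patient and retains the induction sample, because the comparison with baseline depends on it.
- State in Table 1 that the enzyme criterion counts only when the value is above threshold and also higher than the patient's induction value.
- State that the ECG criterion counts only for a specified ischemic change that is new from the preoperative ECG.
- Leave the two criteria as alternatives; this correction does not need both to be met.

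The cost is the wording of one row in Table 1 and the reconciliation of one row in Table 3 with the text. The preoperative ECG and the induction sample are already planned in Measurements. The downside is a somewhat lower event rate for this component. The article says that enrolment began in 2007, so events already recorded should be re-read under the revised rule, blind to assignment. Any patient without an induction sample should be identified.
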